### Outcome measures

#### Primary outcome measure

As the primary outcome measure, B-mode ultrasonography will be used to measure facial expression muscle thickness ratio of affected/healthy side.

The operator will use the muscle thickness of both sides of frontal muscle and depressor anguli oris muscle to calculate the affected/healthy side ratio.
Four test points will be on both sides of the frontal muscle and depressor anguli oris muscle (Fig. 5).Detailed procedure: The examination will be performed in a quiet room with low light and at constant room temperature. Participants will lay still for 5 minutes before test. During measurements, participants will lay on the examination bed on their back, keeping their mouths closed and relaxed without making any other expression. An experienced B-mode ultrasonographer will take all measurements.Equipment: GE Logiq9 real-time ultrasonic diagnostic instrument will be used to obtain the measurements. M12L will be used as the probe at a frequency of 5~14MHz and a main frequency of 10MHz.Timepoint of the test: Two measurements will be taken: pre-treatment and at follow-up 1 (week 10).

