**Methods:**

This is a patient-assessor blinded, randomized, sham-controlled trial. A total of fifty-six eligible patients will be randomly divided into TEA (n=28) and sham TEA (STEA) (n=28) groups. Both groups will receive TEA or STEA treatment at the frontal muscle and the depressor anguli oris muscle, at one predefined points once a week for eight weeks. Additionally, both groups will receive traditional acupuncture treatment at ten acupoints (GB20, LI4, LR3, GB12, ST7, SI18, LI20, BL2, SJ23, ST4) twice a week for eight weeks as a concurrent treatment. B-mode ultrasonography will be used to assess the changes in facial expression muscle thickness ratio of the affected/healthy side at baseline and at 10 weeks after screening, as the primary outcome. House-Brackmann Grade and lip mobility score will be measured and analyzed at baseline and 4, 8, 10, and 12 weeks after screening, as secondary outcomes.

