### Study design

This is a patient-assessor blinded, randomized, sham-controlled efficacy trial on TEA for alleviating FEMA after PFP. A total of fifty-six eligible participants will be recruited from the inpatient and outpatient departments of the First Affiliated Hospital of Zhejiang Chinese Medical University. They will be assigned randomly into either the TEA or STEA group. Patients in both groups were given TEA (for TEA group), or STEA (for STEA group), and traditional acupuncture treatments (for both groups) for eight weeks. Regular follow-up will be conducted for up to four weeks after the intervention.

B-mode ultrasonography will be used to assess the changes in facial expression muscle thickness ratio of the affected/healthy side at baseline and 10 weeks after screening as the primary outcome. House-Brackmann Grade (H-B Grade) [24] and lip mobility score [25] will also be measured and analyzed at baseline and 4, 8, 10, and 12 weeks after screening, as secondary outcomes (Figs. 1, 2). The study protocol was approved by the Ethics Committee of the First Affiliated Hospital of Zhejiang Chinese Medical University on the Use of Human Subjects for Teaching and Research (approval No.2020-K-084–01) and registered in the Chinese Clinical Trial Registry (ChiCTR1900027170). The study design followed the Standard Protocol Items of Recommendations for Interventional Trials (SPIRIT) Checklist (Additional file 1).

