### Sample size

The sample size was based on previous similar studies [26], and advice from an expert group. The formula below was used to determine the sample size in each group (28 participants) (alpha (significance level), power (1-beta), dropout rate, and group sample ratio were 0.05, 0.90, 10%, and 1:1, respectively). σ indicates standard deviation (23.30) and d represents the mean difference between the two groups (21.54):
$$ \mathrm{n}=2{\sigma}^2{\left({\mathrm{Z}}_{\alpha /2}+{\mathrm{Z}}_{\beta}\right)}^2/{\mathrm{d}}^2 $$

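### The primary metric is not fixed (thickness ratio or its change), the sample-size SD is tied to neither, and the chi-square test named for it fits neither

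*Protocol article*

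**What the plan says.** Four parts of the Protocol article bear on the primary comparison.

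- **Abstract (Methods) and Study design** name a change. The Study design section says the trial will "assess the changes in facial expression muscle thickness ratio of the affected/healthy side at baseline and 10 weeks after screening as the primary outcome", and the Abstract is worded almost identically.
- **Primary outcome measure** names the ratio: "As the primary outcome measure, B-mode ultrasonography will be used to measure facial expression muscle thickness ratio of affected/healthy side". On timing it adds "Two measurements will be taken: pre-treatment and at follow-up 1 (week 10"). It does not say whether arms are compared on the week-10 value or on the difference between the two measurements.
- **Sample size** uses the two-means formula, where "σ indicates standard deviation (23.30) and d represents the mean difference between the two groups (21.54"). No outcome, unit or time point is attached to either figure. The source is given only as "The sample size was based on previous similar studies [26], and advice from an expert group".
- **Data processing and statistical analysis** assigns a chi-square test to the primary outcome and keeps the independent-samples t-test for continuous secondary outcomes. For the primary outcome it gives no responder cut-off, change score or baseline adjustment.

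**The concern.** The week-10 ratio and the change in the ratio are both legitimate endpoints, and under randomisation both have the same expected difference between arms. Their variances differ, however, so one SD cannot in general serve both. On the same data, one can reach p<0.05 when the other does not. A power statement therefore means something only once the metric is named and the SD is known to belong to it. Here neither condition is met.

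The stated test does not help. A chi-square test compares proportions, and the plan defines no categories of the ratio. The sample size was computed for a difference in means, so the planned power does not describe the named test at all.

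Baseline matters as well. With about 25 to 28 patients per arm, a chance baseline difference carries over in part to the week-10 comparison and, with opposite sign, to the change comparison. The baseline ratio is measured in every patient, but the stated primary test does not use it.

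**Working it through.** **Inputs from the Sample size section:** SD 23.30; difference 21.54; two-sided alpha 0.05 (the formula uses Z for alpha/2); power 0.90; dropout 10%; allocation 1:1.

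**Assumptions, not in the documents:** correlation r between the baseline and week-10 ratio, taken as 0.3 to 0.7; equal variance at the two times unless stated; 23.30 and 21.54 are on the scale of the ratio or its change.

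**1. The plan's own figure.** n = 2 × 23.30² × (1.960 + 1.2816)² / 21.54² = 24.59, so 25 per arm. 25 / 0.9 = 27.8, so 28 per arm. The stated size reproduces. With 25 evaluable per arm, power is 90.5% by the normal approximation and 89.3% by the noncentral t.

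**2. Power for the version whose SD is not 23.30.** With equal variances, SD(change) = SD(ratio) × √(2(1 − r)). Noncentral-t power, 25 per arm, difference 21.54:

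| r | If 23.30 is the ratio's SD: SD of change | Power on change | If 23.30 is the change's SD: SD of ratio | Power on week-10 ratio |
|---|---|---|---|---|
| 0.3 | 27.57 | 77% | 19.69 | 97% |
| 0.5 | 23.30 | 89% | 23.30 | 89% |
| 0.7 | 18.05 | 98.5% | 30.08 | 70% |

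The gap can go either way.

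**3. Dependence on the equal-variance assumption.** In general Var(change) = s0² + s1² − 2·r·s0·s1, with s0 the baseline SD and s1 the week-10 SD. This equals s1² when r = s0/(2·s1). With equal SDs the break-even is r = 0.5. With s0 = 0.6·s1 it is r = 0.3, where both versions have 89% power if 23.30 is the week-10 SD. The entry criterion capping the ratio at 90% may make s0 smaller than s1, so the table is illustrative only.

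**4. Disagreement between the versions.** Trials were simulated with a t-test on each version (40,000 per scenario, planned effect, 25 per arm, equal variances). If 23.30 is the ratio's SD, the two tests disagreed at p<0.05 in 20%, 14% and 11% of trials at r = 0.3, 0.5 and 0.7. If it is the change's SD, they disagreed in 10%, 14% and 29%.

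**5. Baseline-adjusted comparison.** ANCOVA has residual SD = SD(ratio) × √(1 − r²). If 23.30 is the ratio's SD, this is 22.23, 20.18 and 16.64 at r = 0.3, 0.5 and 0.7, giving power of 92%, 96% and 99%. If 23.30 is the change's SD, the residual SD is 18.79, 20.18 and 21.48, giving 98%, 96% and 93%. Within this range, ANCOVA is above both unadjusted versions. With baseline as covariate, replacing the week-10 value by the change shifts only the baseline slope, by one; the treatment estimate is unchanged.

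**The case against.** The strongest reply is that the sections do not truly conflict. The outcome section describes how the variable is measured, the Abstract and Study design say how it is used, and two measurements are exactly what a change score needs. That reading is fair, and no section says the outcome is the week-10 value alone. A reader might infer a flat contradiction, but the documents support only a metric that is not stated consistently. The reply does not settle what 23.30 and 21.54 describe, nor does it rescue the chi-square test.

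A reader might also infer that the trial is underpowered, or that 90% power holds only if r is 0.5. Neither is supported. The correlation, the two variances and the meaning of 23.30 are all unstated, the direction of any error is unknown, and the 0.5 figure requires equal variances.

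Nor do the documents say that the metric will be chosen after the data are seen, so an inflated false-positive rate from picking the better of two tests is a hypothetical risk and not a feature of the plan. The t-test figures likewise describe what the sample-size formula implies, not the chi-square test actually named.

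Finally, covariate adjustment is often left to an analysis plan, and the source of the SD may be explained in a fuller protocol. So the missing covariate alone would be no finding. But the article does name a primary test, that test does not fit the outcome, and ANCOVA is offered as its replacement.

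**Conclusion.** The point holds as an unfixed primary metric with a mismatched test. The sample-size arithmetic is correct. The planned power of about 90% (89% by noncentral t, 25 per arm) belongs to a two-means comparison of whichever version has SD 23.30, and to nothing else in the plan.

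For the other version, power runs from 77% to 98.5% if 23.30 is the SD of the ratio, or from 97% down to 70% if it is the SD of the change. Both ranges rest on assumed correlations of 0.3 to 0.7 and equal variances. At the planned effect, the two versions would disagree on significance in roughly 10% to 29% of trials under those assumptions. The chi-square mismatch needs no assumption and follows from the text. The point should be corrected, but it does not show that 28 per group is too few.

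**What to change.** - In the Abstract, Study design and Primary outcome measure sections, state one primary metric in the same words: either the affected/healthy thickness ratio at week 10, or its change from baseline to week 10.
- In the analysis section, replace the chi-square test for the primary outcome with ANCOVA: the arms compared with the baseline ratio as covariate. The treatment estimate is then the same for value or change, so the choice of metric no longer affects the result.
- In the Sample size section, say which quantity and unit 23.30 and 21.54 describe, and restate the power for the ANCOVA with the assumed correlation shown.

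The cost is wording in these five places and one degree of freedom. The baseline ratio is already collected, so no patients, visits or measurements are added. The trial measures two muscles, and this change does not by itself say how their ratios enter the primary comparison; the revised definition should make that clear too.

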#### Inclusion criteria

Patients will be eligible for the study if they:
Male or female patients aged 18–65 years.Patients diagnosed with peripheral facial paralysis ≥3 months before screening.Patients with H-B Grade ≥III.Patients with atrophic facial expression muscles as revealed by B-mode ultrasonography. The muscle thickness of the affected side/healthy side ≤ 90%.

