### Data processing and statistical analysis

Following the intention-to-treat principle, data processing and analysis will be performed at the Clinical Evaluation and Analysis Centre of The First Affiliated Hospital of Zhejiang Chinese Medical University. These analyses will be performed on the base of a full analysis set (FAS) and a per-protocol set (PPS). All efficacy analyses will be performed using a FAS, which will consist of all patients who passes the randomized stage and who receives at least one intervention. Last observation carried forward (LOCF) analysis will be used for missing data imputation. The PPS will be considered as a supportive analysis. The results of FAS and PPS analyses will be compared to ensure that the results are consistent. A generalized linear mixed-effect model will be used for sensitivity analysis via the PPS. A subgroup analysis will be conducted following the Kellgren–Lawrence grade.

Quantitative results will be described by the mean, standard deviation, median (quartile 3–1, Q3–Q1), minimum, and maximum, while qualitative results will be expressed as total number and percentages. Grade results with rank meaning will be described via both quantitative and qualitative methods.

The chi-square test will be used to compare the primary outcomes between the two groups. The Wilcoxon rank-sum test will be used to compare ranked data and the independent samples t-test for secondary outcome measures to analyze continuous variables. The incidence of adverse events will be determined and compared between the two groups for safety outcomes. A p-value of <0.05 will be considered statistically significant. SPSS Statistics V.22.0 will be used for all analyses. An interim analysis will be conducted when 50% of the randomized patients completed the primary outcome measurement.

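### The protocol does not fix how two muscles form the one primary ratio, which leaves room for two unadjusted primary tests

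*Protocol article*

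**What the plan says.** All references are to the protocol article.

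- **Primary outcome measure.** The outcome is named in the singular: "B-mode ultrasonography will be used to measure facial expression muscle thickness ratio of affected/healthy side". The measurements cover two muscles: "Four test points will be on both sides of the frontal muscle and depressor anguli oris muscle". The derivation is given in one sentence: "The operator will use the muscle thickness of both sides of frontal muscle and depressor anguli oris muscle to calculate the affected/healthy side ratio". Measurements are taken before treatment and at week 10.
- **Abstract and Study design.** Both also name a single primary outcome, the affected/healthy thickness ratio.
- **Data processing and statistical analysis.** One test is assigned to "compare the primary outcomes between the two groups", in the plural. One general threshold of p<0.05 follows, with no adjustment. An interim analysis is planned once half of the randomised patients have the primary measurement.
- **Sample size.** One difference (21.54) and one standard deviation (23.30) are used. The other inputs are "alpha (significance level), power (1-beta), dropout rate, and group sample ratio were 0.05, 0.90, 10%, and 1:1, respectively". No muscle, and no combination of muscles, is attached to these figures. The result is 28 per group.
- **Inclusion criteria.** Entry depends on the same kind of ratio, in per cent: "The muscle thickness of the affected side/healthy side ≤ 90". Again no muscle is named.

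**The concern.** Two muscles on two sides give two natural affected/healthy ratios per patient and visit. Several primary variables fit the text: the frontal ratio, the depressor anguli oris ratio, the mean of the two, the ratio of summed thicknesses, or both ratios tested side by side. These are different variables. The mean of ratios weights the muscles equally, while the ratio of sums gives the thicker muscle more weight.

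Two things are at stake. First, the choice can be made after data have been seen, including at the interim analysis, and the plural in the analysis section leaves room for two primary tests at 0.05 with success on either. Second, if one muscle improves and the other does not, the plan does not say whether the trial is positive.

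The entry rule has the same gap. If a low ratio in either muscle suffices, a patient with atrophy in one muscle only can be enrolled, and the other muscle then has little room to improve.

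**Working it through.** **1. Reproduce the stated sample size.** Inputs from the Sample size section: SD 23.30, difference 21.54, two-sided alpha 0.05 (the formula uses Z at alpha/2), power 0.90, dropout 10%.

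n = 2 × SD² × (Z₀.₉₇₅ + Z₀.₉₀)² / d² = 2 × 23.30² × (1.960 + 1.2816)² / 21.54² = 24.59, so 25 evaluable per group.

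Dropout: 25 / 0.9 = 27.8, so 28 per group. The stated figure reproduces, and it covers exactly one comparison.

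**2. False-positive rate if each muscle is tested at two-sided 0.05 and either suffices.** With independent tests this is 1 − 0.95² = 0.0975. For correlated tests it is 1 − P(|Z₁| < 1.96 and |Z₂| < 1.96), with (Z₁, Z₂) bivariate normal. The protocol gives no correlation, so a range is shown.

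| Between-muscle correlation | Either test significant |
|---|---|
| 0 | 9.75% |
| 0.3 | 9.5% |
| 0.5 | 9.1% |
| 0.7 | 8.3% |
| 0.8 | 7.8% |
| 0.9 | 7.0% |

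These rates count errors in both directions. Counting only false claims that favour thread embedding, the rate is 4.9% at correlation 0 and 3.5% at 0.9, against 2.5% for one test. No inflation from the interim look is included.

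**3. Other readings of the same text.** One combined ratio tested once has a rate of 5%. If both muscles must be significant, the rate is at most 5%, but power falls. With 25 evaluable per group and the same difference and SD for each muscle, joint power is 81.8% at correlation 0 and 86.2% at 0.8, against 90.5% for a single test.

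**4. Power if separate claims per muscle are wanted.** Standardised difference with 25 per group: 21.54 / (23.30 × √(2/25)) = 3.27.

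- At alpha 0.05: Φ(3.27 − 1.96) = 90.5%.
- At alpha 0.025: Φ(3.27 − 2.24) = 84.8%.
- For 90% per test at 0.025: 30 evaluable per group, and 30 / 0.9 = 33.3, so 34 per group (68 in total).

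**5. Effect of averaging.** Suppose 23.30 is the SD of one muscle's ratio and the two SDs are equal. The mean then has SD 23.30 × √((1 + ρ)/2), which is 20.2 at ρ = 0.5. For the same difference, n = 24.59 × 0.75 = 18.4, so 19 evaluable per group. At ρ = 1 the SD is again 23.30 and n is 25. On these assumptions averaging never needs more than the planned number.

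**6. Entry threshold.** A patient at 80% in one muscle and 100% in the other has a mean of 90%, which satisfies the threshold. Applying the threshold to the mean makes it consistent with a mean-based primary variable, but does not exclude atrophy in one muscle only.

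**The case against.** The strongest reply is that the text points to one ratio. The outcome section, the Abstract and the Study design all use the singular, and the sample size has one difference and one SD. Against this stands a single plural in a condensed analysis paragraph. This is also a journal article, and a multiplicity rule is routinely left to an analysis plan that is not shown.

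Much of this stands. A reader might infer that the trial will run two primary tests, each at 0.05, and so carries a false-positive rate of 9–10%. The documents do not support that. They nowhere say that each muscle is tested or that a result on either one is enough; the 0.05 threshold is stated once, in general terms; and 9–10% also needs a correlation of about 0.5 or less. A reader might also want to put a figure on the power lost through patients with atrophy in one muscle only. The protocol gives neither the proportion of such patients nor the muscle to which the difference and SD apply, so no figure can be derived.

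The absence of a multiplicity rule is therefore not the point. What remains is the definition of the primary variable. The section that defines it goes down to probe frequency and still does not say how two muscles become one ratio. The same undefined ratio decides eligibility, which is being applied now; a later analysis plan cannot settle that for patients already enrolled.

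**Conclusion.** The concern holds as a gap in the definition of the primary variable. The protocol does not fix how the two muscles form the primary ratio, refers to primary outcomes in the plural without adjustment, and sizes the trial for one comparison. As written, two unadjusted primary tests are permitted though not stated, and disagreement between the muscles has no defined outcome.

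The size is conditional. The false-positive rate is about 7.0% to 9.75% if both muscles are tested separately, either counts as success, and the correlation lies between 0.9 and 0. It is at most 5% under one combined ratio or a both-must-succeed rule. The 28 per group is correct for a single comparison. The definition should be settled because it is a choice that could otherwise be made with data in view.

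**What to change.** Before the interim analysis or any unblinding, whichever comes first, define one primary variable. For example: the per-patient mean of the frontal and depressor anguli oris affected/healthy ratios at week 10, compared between groups once at two-sided 0.05 with the baseline mean as covariate. Report each muscle as secondary, and change the plural in the analysis section to match. The chi-square test named there for the primary comparison would be replaced by this analysis. A single named muscle would also close the gap; what matters is that the choice is fixed in advance.

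If separate claims per muscle are wanted, use Holm (the smaller p-value at 0.025, the other at 0.05) and restate the power: about 85% per test at 0.025 with 25 evaluable per group, or 34 per group to keep 90%, assuming the same difference and SD for each muscle.

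State which ratio the 90% entry threshold refers to, so that it is consistent with the primary variable, and record how it has been applied so far.

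Cost: no new measurements, and no increase in sample size for a single primary variable on the plan's own inputs. The downside is that single-muscle results become secondary. The eligibility clarification may need more than wording. The Modification of the protocol section requires a formal application for changes to the patient population, and the Trial status section reports recruitment since October 2020 with ten patients under treatment.

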**Fig. 5 Fig5:**
[figure not shown]
Location of the four operation points

#### Secondary outcome measures

House-Brackmann Grade, the severity of facial paralysis will be assessed using the HB Grade at weeks 0, 4, 8, 10, and 12. Grade I (normal function) to VI (total paralysis) will be evaluated based on the facial function at rest and with effort.Lip mobility score. Lip mobility will be assessed using the lip-length index (LL-index) and snout index (S-index) at weeks 0, 4, 8, 10 and 12. The LL-index will be calculated by determining the percentage change in lip length between grinning and resting. The S-index will be calculated by determining the percentage change in lip length between puckering and resting. Lip length will be measured by determining the inter-commissural length.

